# Sub-symptom threshold aerobic exercise for patients with persisting post-concussion symptoms and exercise intolerance after mild traumatic brain injury – a study protocol with a nested feasibility study for a randomized controlled trial

**DOI:** 10.1186/s12883-023-03221-7

**Published:** 2023-05-03

**Keywords:** mTBI, Exercise intolerance, Buffalo Concussion Treadmill Test, Sub-symptom threshold aerobic exercise, Persistent post-concussion symptoms

## Abstract

**Background:**

Persistent post-concussion symptoms (PPCS) affect between 34 and 46% after a mild traumatic brain injury (mTBI). Many also experience exercise intolerance. Sub-symptom threshold aerobic exercise, SSTAE (exercise at an intensity level that does not increase symptoms) is proposed as a treatment to both reduce the symptom burden and increase the exercise tolerance after the injury. It is unclear if this also applies in a more chronic phase after mTBI.

**Main purpose:**

The main purpose of this study is to evaluate whether SSTAE in addition to ordinary rehabilitation will lead to clinically meaningful improvement of symptom burden, normalize exercise tolerance, increase physical activity, improve health-related quality of life, and reduce patient-specific activity limitations compared to a control group that only receives ordinary rehabilitation.

**Design:**

Randomized, controlled, single-blind parallel-group study with three measurement times; T0 at baseline, T1 after the intervention and T2 six months after T1.

**Methods:**

Patients between the ages of 18 and 60 with exercise intolerance and persistent PPCS (> 3 months) will be recruited to the study and randomized to two groups. All patients will receive follow-up at the outpatient TBI clinic. The intervention group will in addition receive SSTAE for 12 weeks with exercise diaries and a retest every 3 weeks for optimal dosage and progression. The Rivermead post-concussion symptoms questionnaire will be the main outcome measure. The secondary outcome measure will be a test of exercise tolerance—the Buffalo Concussion Treadmill Test. Other outcome measures include the patient-specific functional scale that measures patient-specific activity limitations, as well as outcome measures for diagnosis-specific health-related quality of life, anxiety and depression, specific symptoms such as dizziness, headache and fatigue, and physical activity.

**Discussion:**

This study will add knowledge about the effect of SSTAE and whether it should be implemented in rehabilitation for the adult population with persistent PPCS after mTBI. The nested feasibility trial showed that the SSTAE intervention was safe and that the study procedures and delivery of the intervention overall were feasible. However, minor amendments to the study protocol were made prior to the commencement of the RCT.

**Trial registration:**

Clinical Trials.gov, NCT05086419. Registered on September 5th, 2021.

**Supplementary Information:**

The online version contains supplementary material available at 10.1186/s12883-023-03221-7.

## Background

Exercise, as a rehabilitation intervention for patients with persistent symptoms after mild traumatic brain injury (mTBI), will be explored in this randomized controlled trial (RCT). Traumatic brain injury (TBI) is a complex injury defined as a change in brain function or other signs of brain pathology caused by an external force [1]. Between 80–90% are mTBI, with an annual incidence in Norway of 302 pr. 100,000 [2].

The most common causes of mTBI injuries are falls, traffic, sports related accidents and violence [3–5]. Many recover well during the first three months after the injury, but between 34 and 46% report cognitive, psychological, and physical persistent post-concussion symptoms (PPCS) at three and six months [6]. More specifically, headache, dizziness, fatigue, emotional distress, problems with memory, concentration and slowed thinking are common PPCS [6, 7]. In addition, exercise intolerance, PPCS exacerbation during physical activity, is challenging to manage. Because many patients with mTBI are young and of working age [2], it is important to develop effective rehabilitation interventions.

Traditionally, mTBI management has consisted of advice on physical and cognitive rest until the PPCS wanes, and then gradually resume activities [7–9]. However, this approach is questioned [7] as studies show no effect of rest on PPCS after mTBI [10–12]. Studies rather suggest that cognitive and physical rest beyond the first few days contributes to persistent PPCS [8, 11]. PPCS might also reduce activity and participation, and is associated with reduced health-related quality of life [13]. Hence, a more physically active approach in rehabilitation after mTBI should be explored [8, 9, 14].

Studies indicate that both central and systemic physiological dysfunction can contribute to exercise intolerance after mTBI [9, 14]. Exercise intolerance can be understood as reduced ability to be physically active/exercise at the expected level according to age and physical condition due to exacerbation of symptoms [14–16]. Research suggests that metabolic and physiological changes in the acute phase after mTBI may lead to autonomic dysfunction and abnormal control of cerebral blood flow. This can cause increased symptoms (e.g., headache and dizziness) with exertion and lead to exercise intolerance [9, 14]. The risk of developing exercise intolerance with symptom exacerbation during physical activities is believed to increase 3–18 times after mTBI compared to healthy controls [14, 15]. However, it is unclear whether this also applies in a more persistent phase after mTBI.

Aerobic exercise at an intensity level that does not increase symptoms (sub-symptom threshold aerobic exercise, SSTAE) has received increasing focus in rehabilitation of patients with PPCS after mTBI. Recent studies suggest that SSTAE is safe, reduces PPCS, and may contribute to fewer activity limitations and increased participation [7, 17, 18]. However, studies utilizing an adapted exercise program have mainly studied young athletes [7, 19] or general instructions about physical activity to the mTBI adult population in the acute phase as mean to prevent PPCS [20]. The Buffalo Concussion Treadmill Test (BCTT) is a safe and validated treadmill test that has been developed to evaluate exercise intolerance after mTBI [8, 9, 21, 22]. The BCTT is designed to identify symptom exacerbation thresholds while SSTAE may be utilized to guide the exercise intensity based on the symptom threshold, i.e., sub-symptom exercising [8, 9, 14, 15, 17, 21–23].

To our knowledge, no larger clinical trials determining the effects of SSTAE in patients suffering from exercise intolerance and PPCS after mTBI in the general adult population have currently been concluded [7, 24]. Hence, there is a lack of evidence-based knowledge about the effect of SSTAE in adult patients in a more chronic phase after the injury. Few larger studies with control groups have made it difficult to draw good evidence-based guidelines for clinical practice [7]. Thus, there is a need for randomised clinical trials (RCT) testing the effect of SSTAE in the adult population with PPCS. The main purpose of this study is to explore the effect of SSTAE on PPCS and exercise intolerance in patients with mTBI compared with a control group receiving treatment as usual (TAU) only.

## Objectives

The aim of this study is to explore whether SSTAE, in addition to TAU, will reduce symptom burden and normalize exercise tolerance compared with a control group that only receives TAU.

Further, we aim to evaluate the effect of SSTAE on changes in symptoms such as headache, fatigue, anxiety, and depression, and to register changes in physical activity, health-related quality of life and patient-specific activity limitations.

Our specific hypotheses are:H1: The SSTAE intervention will result in a greater reduction in PPCS symptom burden compared with TAU only.H2: The SSTAE intervention will result in a greater normalisation of exercise tolerance compared with TAU only.H3: The SSTAE intervention will result in greater improvement in headaches, fatigue, anxiety, depression, physical activity, and health-related quality of life compared with TAU only.H4: The SSTAE intervention will result in greater improvement in patient-specific activity limitations compared with TAU only.

In accordance with the New Medical Research Council guidelines [25] we conducted a feasibility study as a preparatory step before initiating the RCT. The feasibility study is nested in this protocol article. The aim of the feasibility study was to evaluate the intervention arm using predefined success criteria shown in Table 2.

### Trial design

This is as a randomized, controlled, single-blind clinical trial with two parallel groups allocated with a 1:1 ratio, and a primary endpoint of difference in PPCS burden at 12 weeks. See Table 1 for Standard Protocol Items: Recommendations for Interventional Trials (SPIRIT) [26, 27].

**Table 1 Tab1:** Standard Protocol Items: Recommendation for interventional Trials (SPIRIT) of the current randomized controlled trial

		**STUDY PERIOD**				
	**Enrolment**	**Baseline test**	**Allocation**	***Intervention***	**Assessments**	
**TIMEPOINT**		***T***_***0***_			***T***_***1***_*** (12 weeks)***	***T***_***2***_*** (6 months)***
**ENROLMENT:**						
**Eligibility screen**	X					
**Informed consent**	X					
**Allocation**			X			
**INTERVENTIONS:**						
***SSTAE group***				X		
***TAU group***				X		
**ASSESSMENTS:**						
**Primary outcome measures:** ***Post-concussion symptoms – RPQ***		X			X	X
***Secondary outcome measure:*** **Exercise intolerance – BCTT**		X			X	X
***Other outcomes***		X			X	X

*Abbreviation*: *SSTAE* Sub-symptom threshold aerobic exercise, *TAU* Treatment as usual, *RPQ* Rivermead Post-concussion symptoms questionnaire, *BCTT* Buffalo Concussion Treadmill Test

Patients referred to the TBI outpatient clinic will be screened for eligibility by the treating physician and invited to participate in the study. Informed consent will be collected and baseline assessment (T0), including patient reported outcome measures and test of exercise tolerance, will be conducted (Table 3). After the baseline assessment, participants will be randomized to SSTAE intervention or TAU group. Further, follow-up testing will be carried out after the intervention period at 12 weeks (T1) and 6 months (T2) after the baseline assessment.

The nested feasibility study was a non-randomized, feasibility study of the intervention arm of the RCT, and included baseline assessment and follow-up after 12 weeks of SSTAE. According to the predefined success criteria, we assessed the recruitment process, retention rates, outcome measures, and adherence to the intervention. A convenience sample including 11 patients with mTBI and self- reported exercise intolerance was recruited to the feasibility study from October – November 2021.

## Methods: patients, interventions, and outcomes

### Study setting

The clinical trial will be carried out at the TBI outpatient clinic at the Department of Physical Medicine and Rehabilitation, Oslo University Hospital (OUH), the trauma referral centre in South-East Norway [28]. Patients are referred to the TBI outpatient clinic from the Emergency department, Neurosurgical department, and from general practitioners. Assessments and clinical testing will be performed in an exercise laboratory at the TBI outpatient clinic. The exercise program will be conducted in the patients’ home setting. The feasibility study was carried out within the same study setting.

### Eligibility criteria

The following inclusion and exclusion criteria will be applied in this trial:

Inclusion criteria: Patients 18–60 years diagnosed with mTBI as defined by the World Health Organization Collaborating Center Task Force [29] with persistent PPCS 3 – 24 months post injury and reduced tolerance of physical activity, defined as self-reported exacerbation of PPCS during physical activity and exercise.Exclusion criteria: Patients with neurological or severe psychiatric conditions documented in the medical record, cardiovascular disease that contraindicates exercise testing [30], extremity injuries that prevent physical exercise, ongoing substance abuse, and insufficient understanding of Norwegian to follow instructions or fill in forms will be excluded before baseline testing. Additionally, patients with no self-reported exacerbation of PPCS during the BCTT will be excluded.In the feasibility study, patients who did not fulfil the stop criteria for the BCTT but experienced symptom exacerbation within 24 h after the test were also included.

### Consent

All patients will receive written and oral information about the study from the treating physician or physiotherapist prior to the baseline assessment and provide their written informed consent. The procedure for obtaining informed consent in the feasibility study was consistent with the current protocol.

## Interventions

### The Buffalo Concussion Treadmill Test—BCTT

The BCTT is the secondary outcome in this trial, but it is also an essential part of the SSTAE intervention and will therefore be described here. The BCTT is a standardized incremental treadmill test designed to identify exercise intolerance and establish symptom thresholds in mTBI patients [17, 21, 22, 31]. The patient walks at a brisk pace on a treadmill (5.2 – 5.8 kph), as incline is increased by 1% each minute. If 15% incline is reached, the speed is increased by 0.3 km/h each minute. The PPCS rated on a 0–10 (best–worst) numerical rating scale (NRS), perceived exertion on Borg Ratings of Perceived Exertion (RPE) 6–20 (lowest to highest) [32], and heart rate (HR) are recorded at the test’s baseline and each minute. The BCTT is terminated when one of three criteria is reached: 1) ≥ 3 points increase in PPCS on the NRS; 2) Borg RPE ≥ 18; 3) 90% of age estimated max HR calculated by (211–0.65 × age) [33]. The first criterium is interpreted as exercise intolerance, and the associated HR is the symptom threshold. The test is considered negative for exercise intolerance if terminated by the intensity criteria, and these patients will be excluded. In the feasibility study, the BCTT was administrated with stop criteria 1 and 2. The third stop criterion was added for the planned RCT to ensure that the participants did not exceed 90% of their estimated HRmax level. We also revised the symptom registration from registration of individual symptoms to registration of an overall PPCS score on the NRS to ensure a total symptom exacerbation of NRS ≥ 3 points.

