**Ancillary non-predefined objectives**	
Patients that report increased PPCS next 24-h after test was included	Patients requires 3-point symptom increase during BCTT to be included
Stop criteria for the BCTT: The patients continued the test until voluntary exhaustion or Borg RPE > 18	Stop criteria BCTT added: 90% estimated max HR (211–0.64*age)
Multiple NRS score per symptom	Overall PPCS NRS, that includes all symptoms that patients relate to PPCS

*PROM* Patient Reported Outcome Measure, *DHI *Dizziness Handicap Inventory, *QOLIBRI* Quality of life after traumatic brain injury, *PPCS Persistent* Post Concussion Symptoms, *NRS* Numerical Rating Scale, *BCTT* Buffalo Concussion Treadmill Test

The results for the primary and secondary outcomes in the feasibility study are presented in more detail in the Supplementary file.

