#### Methods for any additional analyses (subgroups and adjusted analyses

The baseline population, including patients that are excluded due to a negative BCTT, will be described and analysed. Group differences between patients with and without a negative BCTT will be explored. Factors of PPCS and exercise intolerance at baseline will be analysed with multivariable regression analyses. Adherence to the intervention and changes on the BCTT will be described in the intervention group.

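### From a resting NRS of 8 to 10 the BCTT cannot reach its 3-point symptom criterion, so such tests can only be labelled negative, and worsening at rest can score as improvement at follow-up

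*Protocol article*

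**What the plan says.** The BCTT section introduces the symptom score with the words "The PPCS rated on a 0–10 (best–worst) numerical rating scale (NRS" and records it at the start of the test and every minute. For the RCT, scoring of separate symptoms was replaced by "registration of an overall PPCS score on the NRS to ensure a total symptom exacerbation" of at least 3 points. Table 2 (ancillary objectives) describes the new score as "Overall PPCS NRS, that includes all symptoms that patients relate to PPCS".

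The test has three stop criteria. The first is a rise of at least "3 points increase in PPCS on the NRS"; the others are Borg RPE of 18 or more and 90% of estimated HRmax. On the first, the section says: "The first criterium is interpreted as exercise intolerance, and the associated HR is the symptom threshold". On the other two: "The test is considered negative for exercise intolerance if terminated by the intensity criteria, and these patients will be excluded". Table 2 likewise makes a 3-point rise during the test a condition of inclusion.

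The Eligibility criteria section gives no 3-point threshold: "Additionally, patients with no self-reported exacerbation of PPCS during the BCTT will be excluded".

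The BCTT result is used in two further places:
- The secondary endpoint (Outcomes, Secondary outcome) is the change from T0 to T1 in the percentage of estimated HRmax reached and in test duration. The mixed model also estimates the change to T2.
- The section on additional analyses plans that "Group differences between patients with and without a negative BCTT will be explored".

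None of these sections says how a high resting score is handled.

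**The concern.** A rule that needs a fixed rise on a bounded scale stops working near the upper bound. Here the bound lies at the severe end, so the patients who cannot test positive are those with the most symptoms at rest. Per-symptom scoring, as used in the feasibility study, left room for a milder symptom to rise by 3 points. A single overall score does not.

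Three things are at stake:
- **Entry.** Some patients with a high symptom burden are labelled as not exercise intolerant when the test could not have shown otherwise.
- **Follow-up.** The same mechanism can turn worse resting symptoms into a longer test at higher intensity, in either arm.
- **Baseline description.** The comparison of BCTT-negative and BCTT-positive patients would mix people who tolerated the test with people at the top of the scale.

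**Working it through.** **1. The plan's own figure, to see whether it is touched.** Inputs from the Sample size section: SD 8.7, difference 5.0, power 80%, alpha 0.05 (two-sided assumed).

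n per arm = 2 × (1.960 + 0.842)² × 8.7² / 5.0² = 2 × 7.85 × 75.69 / 25 = 47.5, rounded up to 48. The total is 96, and 96 / 0.80 = 120. The stated figures are reproduced. They concern the RPQ and do not depend on the BCTT rule.

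**2. The ceiling.** Inputs from the BCTT section: scale maximum 10, required rise 3, whole-number scoring assumed. Largest possible rise = 10 − resting score.

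| Resting NRS | Largest rise | Can reach 3? |
|---|---|---|
| 0 to 6 | 10 to 4 | yes |
| 7 | 3 | yes |
| 8 | 2 | no |
| 9 | 1 | no |
| 10 | 0 | no |

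For 3 of the 11 scale values the symptom criterion is out of reach. Such a test can end only on Borg RPE or heart rate, and is then negative by definition.

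**3. Who is excluded: the three places side by side.** Take a patient who goes from 8 to 10 and stops on intensity.
- BCTT section: negative, excluded.
- Table 2: no 3-point rise, not included.
- Eligibility criteria: symptoms did get worse during the test, so this exclusion does not apply.

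The same conflict arises at any resting score when the rise is only 1 or 2 points. At 8 or 9 a rise cannot be larger.

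**4. Follow-up.** Anyone randomised under the 3-point rule rested at 7 or less at T0. A resting score that moves from 7 to 8 is enough to remove the symptom stop at T1 or T2. The documents do not say where symptom stops occur. If they occur at 60% to 85% of HRmax (assumed) and the later test runs to 90%, the apparent gain is 90 − 85 = 5 to 90 − 60 = 30 percentage points, with a longer duration. If 2% to 10% of an arm were affected by 10 to 30 points each (assumed), that arm's mean would shift by 0.02 × 10 = 0.2 to 0.10 × 30 = 3.0 points. An equal share and size in both arms would cancel in the group difference.

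**5. Frequency at T0.** No resting NRS distribution is given. Assuming, crudely, a normal score with SD 2, the share at 8 or more (above 7.5) is 1.2% for a mean of 3, 4.0% for a mean of 4 and 10.6% for a mean of 5. These are shares of patients tested at screening. They do not apply to the 120 randomised, for whom the T0 count is zero under the 3-point rule. Nor do they carry over to T1 or T2, because that cohort was selected at 7 or less.

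**The case against.** The strongest reply is that this is an edge case of unknown, possibly zero, frequency that affects a secondary endpoint and an exploratory description. Exclusion comes before randomisation, so it does not bias the comparison of arms. Training intensity is set from the heart rate at the symptom threshold, so a patient with no identifiable threshold lacks that reference, and a new label would not by itself bring such patients into the trial. Worsening is also not hidden: the RPQ is collected at the same visits and resting NRS is recorded at every test. All of this stands, and it limits the size of the point. The feasibility result of 12 of 13 positive tests does not settle the frequency, because it used per-symptom scoring and no heart-rate stop.

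It may also be said that a condensed article leaves edge cases to the test procedure. That has some weight, but the article states the negative label for intensity-terminated tests without exception, and its own passages disagree on who is excluded.

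A reader might infer more: that a participant who worsens to 8 or above is counted as normalised at T1 or T2, with the best possible result. The documents do not support this. H2 speaks of normalisation, but no section defines it by a negative test or carries the positive/negative label to follow-up. The endpoint is continuous, and a Borg stop may come well before 90% of HRmax, so the false gain may be partial or absent. Nor does anything show that everyone resting at 8 or more is truly intolerant; the test simply cannot tell.

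**Conclusion.** The point holds as a defect in a stated classification rule. The ceiling is exact arithmetic: at resting scores of 8, 9 and 10 the BCTT cannot be positive, and calling it negative claims something that the test did not measure. The conflict between the Eligibility criteria and the other two places can be read directly from the text. That worsening at rest can score as improvement on the secondary endpoint follows from the stop rules, on the assumption that the same rules apply at T1 and T2.

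The size is unknown. The ranges shown rest on assumed distributions and only illustrate scale. The effect is confined to who is labelled negative at screening, the secondary endpoint and the baseline comparison of BCTT groups. The primary RPQ endpoint and the sample size of 96 evaluable and 120 recruited are unaffected.

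**What to change.** 1. In the BCTT section, add a sentence such as: *A BCTT that starts at a resting overall NRS of 8, 9 or 10 and ends on an intensity criterion is recorded as not classifiable, not as negative.*
2. In the additional analyses, report these tests as a separate category, apart from the BCTT-negative group.
3. At T1 and T2, keep every observed duration and percentage of HRmax in the main intention-to-treat mixed model. Genuinely recovered participants also stop on intensity, and removing values because of a score measured after randomisation would be selective.
4. Report resting NRS by arm and visit beside the BCTT results.
5. Add one sensitivity analysis that handles values from tests started at 8 to 10 differently, for example set to missing or to the participant's T0 value. Neither choice is neutral, so it should stand beside the main result and not replace it.
6. Reconcile the Eligibility criteria, the BCTT section and Table 2 on who is excluded. No stop rule or eligibility threshold is proposed here.

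The cost is a few sentences, one small extra analysis and a few reclassified tests. No new data are needed, since resting NRS is already recorded at the start of each test.
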